## Methods

### Aims and Objectives

The specific study objectives are to, first, determine and compare the diagnostic agreement between VE and on-screen visual assessment of 3D models in approximate natural colors with and without fluorescence to detect and classify carious lesions on visible tooth surfaces in primary teeth. The second objective is to determine the diagnostic agreement between VE and the automated caries scoring system for detecting and classifying occlusal carious lesions in primary teeth. Finally, the third objective is to explore the impact of caries threshold, tooth surface examined (smooth vs occlusal), and enamel defects’ presence on the reported agreement estimates between caries detection methods.

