### Tooth Surface Exclusion Criteria

Tooth surfaces will be excluded from on-screen assessment if (1) they have a sealant, direct or indirect restoration; (2) the tooth surface visibility on the 3D model is impeded by calculus, debris, or plaque; and (3) less than one-third of the surface is visible due to insufficient or missing scan data.

Tooth surfaces will be excluded from the application of the automated caries scoring system if they (1) have a sealant, direct or indirect restoration; (2) have an enamel defect; (3) are not a primary molar occlusal surface; and (4) less than one-third of the surface is visible due to insufficient or missing scan data.

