### Dental Examination Protocol at the 5-Year-Old Study Visit

#### VE Protocol

VEs occurred with participants in a semisupine position on an adjustable examination bed. The examiner stood to the side of, or behind, the participant. A portable LED light (220 lumens NÄVLINGE clamp spotlight IKEA) and a dental mirror were used and positioned to provide maximum illumination and visibility of the oral cavity without magnification. Cotton rolls and swabs were used to dry teeth and remove plaque. Compressed air was not used. Universal infection control standards and additional COVID-19 precautions were adhered to for all examinations.

Dental examinations were conducted by trained and calibrated registered dental practitioners (BJ and [name]) with experience and prior training in using the ICDAS index in research settings. Examiner BJ is an oral health therapist with 13 years of clinical experience, and examiner [name] is an oral health therapist with 5 years of clinical experience. Before commencing VEs, both examiners had participated in the web-based ICDAS and International Caries Classification and Management System (ICCMS) e-learning modules [26]. Additionally, a senior researcher and pediatric dentist (MS) with experience in conducting surveys using ICDAS and enamel defect indices facilitated a presentation on ICDAS using the ICDAS or ICCMS examiner training materials and training materials for the use of a modified molar incisor hypomineralization (MIH) index to assess for enamel defects (with permission from the author) [27]. A 2-hour calibration session on the application and interpretation of the indices, followed by a computer-based calibration exercise, took place. The computer-based calibration exercises were repeated until both examiners reached an intra- and interexaminer agreement of κ_w_>0.8.

Dental caries experience was recorded for each tooth surface using the 2-digit ICDAS criteria [28]. Code 01 could not be scored for smooth surfaces due to a lack of compressed air. Enamel defects were recorded using a modified MIH index describing each surface’s clinical presentation and the extent of the defect [29]. All tooth surfaces were examined using a systematic approach. The score given was the most severe of the 2 clinical presentations if multiple lesions were present on the same tooth’s surface.

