### Sample Size

This is a retrospective study drawing all eligible participants from the MISBAIR trial who underwent the dental assessment at their 5-year-old study visit.

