A sensitivity analysis will explore the impact of the diagnostic threshold used on agreement estimates. Analyses will be repeated with the caries data dichotomized at alternative thresholds: the moderate and extensive thresholds. In the analysis of the moderate threshold, sound and initial surfaces will be labeled caries absent (0) and all remaining categories (moderate-extensive) will be labeled caries present (1). In the analysis of the extensive threshold, sound, initial, and moderate caries will be combined and labeled as caries absent (0) and only teeth with extensive caries will be marked as caries present (1). To evaluate if the surface location and presence of enamel defects impact the diagnostic agreement estimates, these variables will be included as additional variables in the regression models for the surface-level analyses, including interaction terms with the method. The surface location variable will have 3 levels for each visible tooth surface (occlusal, smooth, and proximal). Enamel defects will be a binary variable, defined as present or absent per person. The sensitivity analysis to compare the agreement between on-screen assessment of 3D models in approximate natural colors and on-screen assessment of 3D models in approximate natural colors featuring fluorescence will include additional variables, rater and timing, as fixed effects.

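### Enamel defects were recorded per surface but are coded per child in the surface-level models, and the automated comparison contains no surface with a defect

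*Protocol article*

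**What the plan says.** Five statements in the protocol article bear on this point.

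- **Aims and Objectives.** Objective 3 is exploratory: "the third objective is to explore the impact of caries threshold, tooth surface examined (smooth vs occlusal"). It also covers enamel defects and their "presence on the reported agreement estimates between caries detection methods". It is not limited to any one pair of methods.
- **VE Protocol.** "Enamel defects were recorded using a modified MIH index describing each" surface, covering both how the defect presents and how far it extends. Surface-level defect data therefore exist.
- **Statistical Analysis, sensitivity paragraph.** For surface location and enamel defects, "these variables will be included as additional variables in the regression models for the surface-level analyses, including interaction terms with the method". Surface location is coded per surface. For defects the rule is different: "Enamel defects will be a binary variable, defined as present or absent per person".
- **Tooth Surface Exclusion Criteria, automated scoring.** Surfaces are removed if they "2) have an enamel defect; (3) are not a primary molar occlusal surface", among other reasons.
- **Tooth Surface Exclusion Criteria, on-screen assessment.** The list opens "Tooth surfaces will be excluded from on-screen assessment if (1) they have a sealant, direct or indirect restoration; (2) the tooth surface visibility" and ends with insufficient scan data. An enamel defect is not on it.

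The article gives no reason for the per-person coding. It does not say whether the defect interaction is meant for all the surface-level models or only for the on-screen ones.

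**The concern.** The variable is defined at a different level from the question and from the data. The article treats a defect as a property of a surface when it records it and when it excludes it, since automated scoring loses the affected surface and not the child. In the model the same attribute becomes a property of the child.

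In the on-screen comparisons, a child with one affected surface contributes all of his or her surfaces to the defect-present group. If defects mainly disturb scoring on the surface that carries them, a real effect could appear close to null. In the automated comparison, the per-person flag contrasts children with and without defects on surfaces that have none. Anyone reading that coefficient as the effect of defects on automated scoring would be reading something the data do not contain.

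At stake is the enamel-defect part of Objective 3. Objectives 1 and 2, the main method coefficients, the Bland-Altman analysis and the intraclass correlations do not use this variable.

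**Working it through.** The plan states no figure on this point, and no power, effect size or margin (the sample is all eligible participants: "This is a retrospective study drawing all eligible participants from the MISBAIR trial who underwent the dental assessment at their 5-year-old study visit"). There is nothing to reproduce, so the check has two parts: comparing the rules, then illustrating the dilution on assumed values.

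**1. The rules side by side**

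| Comparison | Surfaces with a defect in the analysis? | What the per-person flag contrasts | What a per-surface flag would contrast |
|---|---|---|---|
| VE vs on-screen, color | Yes | All surfaces of children with vs without any defect | Surfaces with vs without a defect |
| VE vs on-screen, fluorescence | Yes | As above | As above |
| VE vs automated | No, excluded | Unaffected molar occlusal surfaces of children with vs without a defect | Nothing; the variable is constant at absent |

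**2. Size of the dilution, on-screen comparisons**

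Assumed inputs, none of them in the documents:

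- p0, the probability that a surface is scored carious: 0.05 or 0.10. It is taken as the same for VE on all surfaces and for the on-screen method on unaffected surfaces.
- OR, the true surface-level method-by-defect interaction odds ratio: 3, with 2 and 5 as alternatives.
- f, the share of a flagged child's surfaces that carry a defect: 5% to 50%.

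Random effects and zero inflation are ignored.

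Formulas:

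- odds(p) = p / (1 − p)
- probability on affected surfaces: pa = OR × odds(p0) / (1 + OR × odds(p0))
- average over a flagged child's surfaces: pm = f × pa + (1 − f) × p0
- interaction OR shown by the per-person flag = odds(pm) / odds(p0)

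Worked case, p0 = 0.10, OR = 3, f = 10%:

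- odds(p0) = 0.10 / 0.90 = 0.1111
- pa = 0.3333 / 1.3333 = 0.25
- pm = 0.10 × 0.25 + 0.90 × 0.10 = 0.115
- odds(pm) = 0.115 / 0.885 = 0.1299
- flag OR = 0.1299 / 0.1111 = 1.17

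Results:

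| f | Flag OR when true OR is 3 (p0 = 0.10 to 0.05) | Share of the log OR kept (true OR 2 to 5, both p0) |
|---|---|---|
| 5% | 1.08 to 1.09 | 6% to 10% |
| 10% | 1.17 to 1.18 | 13% to 18% |
| 25% | 1.44 to 1.47 | 30% to 39% |
| 50% | 1.91 to 1.95 | 56% to 64% |

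At f = 100% the formula returns the true OR of 3, as it should. A per-surface flag targets that value directly.

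**3. Automated comparison**

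The exclusion rule sets f = 0. Under the same simplified model the flag OR is 1.0 whatever the true effect, so the direct effect of a defect on the scored surface is not estimable under either coding.

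**The case against.** Several counter-arguments have weight.

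- **Affected surfaces remain in both on-screen comparisons.** A reader might infer that the enamel-defect question cannot be answered at all. The documents do not support that: a defect is not an on-screen exclusion, so a child-level association can still be estimated, though diluted. The other parts of Objective 3, caries threshold and surface type, are untouched. This stands.
- **Effects across surfaces are possible.** Nothing in the article says that a defect disturbs detection only on its own surface. The Automated Caries Scoring System section says the software finds a healthy reference within each tooth, so a defect elsewhere on the tooth could plausibly alter the score. This stands, and it limits the automated conclusion to the direct effect on the scored surface.
- **The defect interaction may not be intended for the automated model.** Surface location cannot vary there, since only primary molar occlusal surfaces are scored, so the sentence on additional variables cannot apply to that model in full. This is fair, but the article does not state the limit, and Objective 3 is worded for the methods in general.
- **Confounding by child is limited.** The methods are compared on the same children's surfaces. Child characteristics that shift caries scores equally under both methods go into the defect main effect. Only characteristics that change the difference between methods could distort the interaction. This stands.
- **A per-child variable has a descriptive use.** The article plans to report the proportion of children with defects. That supports keeping such a variable, but not using it as the exposure in a surface-level interaction.
- **No misreporting is announced.** The flag is openly defined as per person, and nothing says a null result would be presented as showing no effect of defects. That remains a risk of interpretation only.

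**Conclusion.** The point holds in a limited form. The recording level and the coding level differ, and the article states both explicitly, so this is a rule fixed badly and not a detail left to another document.

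For VE versus on-screen methods, the interaction is a diluted child-level association. If the effect acts on the affected surface, an assumed true OR of 3 would appear as about 1.1, 1.2 or 1.9 when 5%, 10% or 50% of a flagged child's surfaces are affected. The direction follows from the coding under that assumption. The size rests on assumed values, because the documents give neither the prevalence nor the extent of defects, so no single shrinkage figure can be claimed.

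For VE versus automated scoring, the direct effect of a defect on the scored surface cannot be estimated. The Aims and Objectives, Tooth Surface Exclusion Criteria and Statistical Analysis sections need to be reconciled on this.

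Severity is moderate. The objective is exploratory, the analysis sits in the sensitivity paragraph, and a reader should not infer that the main agreement estimates are compromised.

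**What to change.** 1. In the on-screen surface-level models, define the enamel-defect variable per surface from the recorded index, and interact that variable with method. The per-person flag may be kept as an added child-level covariate.
2. Omit the defect interaction from the VE-versus-automated model.
3. State that the enamel-defect part of Objective 3 applies to the on-screen methods only, and that surfaces with a defect were excluded from automated scoring.

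The cost is a changed variable definition and two clarifying sentences. The surface-level data are already held, so no new examination is needed. The Results section reports that on-screen assessment was still under way, so the change could precede that analysis. Automated scoring was complete by October 2023 and under analysis, so there the step is to leave the interaction out of what is reported.

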### Study Design

This is a diagnostic agreement study, as VE is not considered a gold standard in this setting [23]. Dental caries in this study is defined as primary coronal caries. Data sources (age at dental visit, sex, VE data, and 3D models) will be retrospectively sourced from a sample of children who underwent VE using the ICDAS and intraoral scanning with the TRIOS 4 to produce 3D digital models.

The 3D models for each eligible participant will be subject to an on-screen assessment by 4 qualified dental practitioners. Each practitioner will examine all 3D models at 2 separate time points. An on-screen assessment of 3D models based on tissue geometry and approximate natural colors (excitation to visible white light) will take place first (Figure 1A), followed by an on-screen assessment with the addition of fluorescence texture (excitation to light at 415 nm; Figure 1B). An interval of at least 4 weeks will follow to minimize recall bias before the on-screen assessment process is replicated. Occlusal surfaces of primary molars will be examined using the automated caries scoring system at a single time point only (Figure 1C). Examiners will be blinded to all clinical examination data and automated caries scores when scoring the 3D scans.

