A total of 4 examiners will undertake on-screen assessment. Before commencing on-screen assessment, all examiners will undergo a 2-hour training workshop followed by calibration exercises. Training will focus on applying a merged and modified ICDAS criteria to a data set of 3D models with fluorescence. A dentist and expert in using modified ICDAS to interpret 3D models (SM) will facilitate training. To establish interrater agreement, each examiner will independently undertake an on-screen assessment of a training-calibration data set of 200 examination sites. This data set includes carious lesions and sound surfaces which have been validated histologically as part of a previous study [16,20]. Examiners will repeat this calibration exercise 2 weeks after the initial assessment to establish an intrarater agreement. Examiners will repeat the calibration process until the agreement exceeds κ_w_>0.7.

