### Statistical Analysis

Data checking and cleaning will take place before analysis. Descriptive statistics for patient characteristics such as age, sex, caries prevalence, and the proportion of children with enamel defects will be reported. The total number of tooth sites included in the analysis will be reported.

Descriptive characteristics for the rater population will be reported, including qualification, clinical background, years of experience, and training results for each rater. Interrater and intrarater reliability for on-screen assessment of 3D models based on color and fluorescence using the intraclass correlation coefficient will be reported for all examiners. These estimates will be obtained from a multilevel model fitted to the surface-level data, accounting clustering (see below), and zero inflation.

To assess agreement among methods, we will undertake both surface-level and individual-level analyses. At the surface level, caries data naturally have 3 levels with surfaces clustered within a tooth, which are clustered within an individual. Therefore, for this analysis, we will use multilevel logistic regression to estimate method agreement while accounting for clustering for the tooth. Specifically, separate multilevel models will be fitted to compare VE with each of the alternative methods by including the variable method (VE vs on-screen assessment of 3D models in approximate natural colors, on-screen assessment of 3D models in approximate natural colors featuring fluorescence, and automated system) as the fixed effect. The coefficient estimates for the variable method will be used to indicate the level of agreement. The multilevel model will be fitted with a zero-inflated binomial distribution.

At the individual level, a numerical variable representing the number of lesions per individual will be generated and analyzed with 2 approaches. First, Bland-Altman method agreement analysis will be performed using a regression approach. Specifically, a model will be constructed to regress the difference between each pair of methods on their average [36]. The analysis will be repeated for each possible pair of methods. Second, for each possible pair of methods, an intraclass correlation coefficient will be estimated from a multilevel model fitted to the paired data consisting of the 2 measures for each individual obtained from the 2 methods, fitted with a zero-inflated Poisson distribution.

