## Discussion

This protocol aims to fill a knowledge gap by describing an approach for determining the diagnostic agreement between VE using ICDAS and on-screen assessment of 3D models featuring fluorescence obtained with an IOS.

Intraoral scanning is increasingly being adopted in dentistry as it offers improved clinical workflows for patient assessment and treatment planning, particularly in the disciplines of prosthodontics, orthodontics, and periodontics [13,38,39]. The role of scanning technology in supporting clinical diagnostics is an emerging research area [19,20,40-43]. There is paucity in the literature describing on-screen assessment of 3D models as a method for caries detection.

A strength of our study is the consideration of different approaches to analyze agreement. Our use of multilevel generalized linear regression models to analyze surface-level dental caries data has several strengths. First, caries from the same individual are more correlated than those between individuals. If this clustering is ignored, the estimated variance may be misleadingly small [44]. We will use multilevel models that account for clustering. Second, the multilevel regression approach allows for estimating method agreement while accounting for variability due to the influence of the rater and timing of assessment [45]. Finally, because all eligible primary teeth surfaces will be analyzed the high proportion of sound surfaces will result in zero-inflated outcome data. We will address this by fitting a generalized linear regression framework allowing the use of a zero-inflated binomial distribution; whereas traditional agreement methods, such as the κ statistic, are limited in this context [46]. A limitation of the statistical approach is that the coefficient estimates derived from the multilevel model do not quantify absolute agreement. As an alternative analysis, we will analyze the total caries at the individual level with a regression-based Bland-Altman agreement analysis [36]. The excess of zeros and, hence, the nonnormal distribution of the data precludes the calculation of the limit of agreement estimates that are clinically interpretable. Consequently, we will use the intraclass correlation coefficient derived from a multilevel model fitted with a zero-inflated Poisson distribution, acknowledging that this is influenced by the variability in the population.

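### The colour-versus-fluorescence model gives rater and timing no interaction with method, so it cannot show whether examiners respond differently to fluorescence

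*Protocol article*

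**What the plan says.** The Statistical Analysis section describes the surface-level comparison of the two on-screen modes as a sensitivity analysis whose model "will include additional variables, rater and timing, as fixed effects". Earlier in the same paragraph, surface location and enamel defects enter the surface-level models "including interaction terms with the method". No such term is named for rater or timing. The general surface-level model is meant "to estimate method agreement while accounting for clustering for the tooth", and no random term by rater is stated. How the result will be read is stated plainly: "The coefficient estimates for the variable method will be used to indicate the level of agreement".

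The design is fully crossed. On-Screen Assessment says "A total of 4 examiners will undertake on-screen assessment". Study Design says "Each practitioner will examine all 3D models at 2 separate time points", with colour read first, "followed by an on-screen assessment with the addition of fluorescence texture".

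The Discussion lists as a strength that the multilevel approach "allows for estimating method agreement while accounting for variability due to the influence of the rater and timing of assessment".

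**The concern.** A rater main effect says that one examiner calls more caries than another in both modes alike. A timing main effect says that calls rise or fall between the two rounds in both modes alike. Neither says anything about the difference between modes. What bears on that difference is whether examiners react differently to the fluorescence texture, or change their reaction between rounds. Those are the rater-by-method and timing-by-method interactions.

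The Introduction (Intraoral Scanners for Dental Caries Detection) gives a reason to expect the first: it calls the reading of fluorescence subjective and ties it to the reader's skill and experience.

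The first objective includes comparing the two on-screen modes. The other stated surface-level models each set visual examination against one alternative, so this is the only one that compares colour with fluorescence directly. If some examiners call more lesions with fluorescence and others fewer, the single coefficient tends towards zero, and under the plan's own reading rule that indicates agreement. This can happen for these four examiners alone, without any generalisation.

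**Working it through.** The article states no power, alpha or effect-size calculation for this contrast, so there is no figure to reproduce.

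**Step 1: balance.** From the article: 4 raters × 2 times × 2 modes = 16 readings per surface. Code mode as −0.5 and +0.5. Within each rater the mode codes sum to 2 × (−0.5) + 2 × (+0.5) = 0; within each time they sum to 4 × (−0.5) + 4 × (+0.5) = 0. So the cross-products of mode with the rater and timing indicators are exactly 0, while the mode sum of squares is 16 × 0.25 = 4. In a linear model, main effects of rater and timing cannot move the mode coefficient at all.

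**Step 2: does this carry over to a logistic model?** I used a simulation with 213 children (the article's count for automated scoring, assumed to apply here), 4 raters, 2 times and 2 modes. Assumptions not in the documents: 60 surfaces per child, intercept −4.0, child SD 1.5, rater main-effect SD 0.5, timing effect 0.1, mean mode effect 0.3, and rater-by-mode SD from 0 to 0.5, all on the log-odds scale. There were 150 runs per setting. Child effects entered as a known offset; zero inflation and the tooth level were not simulated. Monte Carlo error on coverage is up to about 4 points.

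Adding rater and timing main effects to a mode-only model changed the mean coefficient from 0.295 to 0.298 at SD 0 and from 0.368 to 0.374 at SD 0.5, so by 0.003 to 0.006 over the range. The mean standard error (SE) went from 0.0215 to 0.0217 at SD 0 and from 0.0212 to 0.0214 at SD 0.3.

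**Step 3: cancellation (illustration).** Let the four examiners' mode effects be +0.3, +0.3, −0.3 and −0.3. The mean is (0.3 + 0.3 − 0.3 − 0.3)/4 = 0, although two examiners have an odds ratio of exp(0.3) = 1.35 and two have exp(−0.3) = 0.74. A model with one mode coefficient reports a value near 0.

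**Step 4: the interval, by target.**

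| Rater-by-mode SD | Main-effects SE | Actual SD of estimate over samples of raters | Ratio | Coverage, wider raters: main effects | Coverage, wider raters: fixed interaction | Coverage, wider raters: 4 estimates, 3 df |
|---|---|---|---|---|---|---|
| 0 | 0.0217 | 0.0210 | 1.0 | 0.97 | 0.96 | 0.95 |
| 0.1 | 0.0213 | 0.0576 | 2.7 | 0.49 | 0.57 | 0.91 |
| 0.2 | 0.0214 | 0.1158 | 5.4 | 0.26 | 0.35 | 0.92 |
| 0.3 | 0.0214 | 0.1642 | 7.7 | 0.20 | 0.23 | 0.95 |
| 0.5 | 0.0212 | 0.2610 | 12.3 | 0.11 | 0.13 | 0.93 |

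A hand check: with 4 raters the expected SD is about √(SE² + SD²/4). At 0.2 this is √(0.0217² + 0.04/4) = 0.102, close to the simulated 0.116.

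A second simulation (80 surfaces per child, rater SD 0.3, surface random intercepts, discordant-pair analysis) gave an SE near 0.024 against an actual SD of 0.054, 0.103 and 0.147 at rater-by-mode SD 0.1, 0.2 and 0.3.

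**Step 5: these four examiners only.** For the simple average over the four sampled raters, the fixed-interaction model covered 0.92 to 0.96 throughout. The main-effects model covered 0.97, 0.90, 0.75, 0.62 and 0.43. Its SE is not the cause: when raters differ in how often they call caries, the single logistic coefficient weights them unequally and so estimates a different average. This loss depends on the assumed rater SD of 0.5.

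**The case against.** - **The text is silent on interactions rather than excluding them.** Describing rater and timing as fixed effects sets them apart from random effects, and an article condenses its model terms. Objective 3 also explains why surface location and enamel defects get interactions. This limits the point to what is stated. But the same paragraph spells out interactions for two variables and not for the other two, and the Discussion claims a benefit that the stated terms do not provide.
- **Rater disagreement is handled elsewhere.** Inter- and intrarater intraclass correlations are planned for both modes, and examiners repeat calibration until weighted kappa exceeds 0.7. Both are useful. Neither enters the mode coefficient, and neither shows which way each examiner moves when fluorescence is added.
- **Fixed effects for four raters are defensible.** This stands. They conventionally target the raters in the study, and a random-slope variance from four raters would be poorly estimated, so a random slope should not be required.
- **The error bars are simply too narrow.** A reader might infer this, but the documents do not support it without conditions. It needs examiners who differ in their response and inference beyond these four; with no such variation the SE is right.
- **The analysis has an inflated false-positive rate.** A reader might infer this too. The article states no null hypothesis, alpha or test for this contrast, so there is no planned error rate to inflate.

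**Conclusion.** The point holds as a cheap improvement to one model. In the stated design, rater and timing main effects leave the mode coefficient and its SE practically unchanged. The model therefore cannot detect examiner-specific responses to fluorescence, opposite responses can pass as agreement, and the Discussion's claim is not met for this contrast. This rests on the crossed design and on reading the absence of a named interaction as its absence from the model. Surface exclusions could disturb the balance slightly.

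The effect on the interval is conditional. For a wider population of examiners the SE would be about 2.7 to 12 times too small at rater-by-mode SDs of 0.1 to 0.5. Those SDs are assumptions, since the documents give no value, and neither simulation fitted the planned zero-inflated multilevel model. The comparisons with visual examination are not touched by this point.

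**What to change.** In Statistical Analysis, for the colour-versus-fluorescence model:

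1. Add rater-by-method and timing-by-method terms, as already done for surface location and enamel defects.
2. Report the four examiner-specific colour-fluorescence differences beside their average.
3. State that the interval for the average applies to these 4 examiners. If the result is to be generalised, base the interval on the spread of the four examiner-specific estimates with 3 df. The fixed interaction alone does not do this: its coverage for wider raters was 0.13 to 0.57 at SD 0.1 or more.
4. In the Discussion, word the statement about rater and timing variability to match the model fitted.

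The cost is a few more model terms and some wording; the readings are already being collected. If the result is generalised the interval becomes wider: in the first simulation the mean SE was 0.052, 0.091 and 0.134 at SD 0.1, 0.2 and 0.3, against about 0.021 with main effects only, and the t multiplier on 3 df is larger as well.
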